### Statistical analysis plan

According to the design of this study, the mixed-effects model will be used to estimate the intervention effect, combined with the causal inference model to deal with non-compliance issues.

#### Establish mixed-effects model to evaluate intervention effect

We will establish a mixed-effects model for open cohorts. To account for the inter-stage and intra-individual correlation decay, we would use the blended correlation decay model for open cohorts proposed by Kasza et al., and use the generalized least squares estimation to estimate the intervention effect [37]. The mixed-effects model is as follows:1$$\left\{\begin{array}{c}{Y}_{ij k}=\mu +{\beta}_j+\delta {X}_{ij}+{\gamma}_{ij}+{\varepsilon}_{ij k}\\ {}{\gamma}_i={\left({\gamma}_{i1},\cdots, {\gamma}_{iJ}\right)}^{\hbox{'}}\sim N\left(0,{\tau}_{\gamma}^2\boldsymbol{M}\left(1,r\right)\right)\\ {}{\varepsilon}_{ik}={\left({\varepsilon}_{i1k},\cdots, {\varepsilon}_{i{J}_kk}\right)}^{\hbox{'}}\sim N\left(0,{\sigma}_{\varepsilon}^2\boldsymbol{M}\left(1,\eta \right)\right),{\boldsymbol{\varepsilon}}_{ik}\perp {\boldsymbol{\varepsilon}}_{im},k\ne m\\ {}\boldsymbol{M}\left({r}_0,r\right)=\left(\begin{array}{ccccc}1& {r}_0r& {r}_0{r}^2& \cdots & {r}_0{r}^{J-1}\\ {}{r}_0r& 1& {r}_0r& \cdots & {r}_0{r}^{J-2}\\ {}\vdots & \vdots & \vdots & \ddots & \vdots \\ {}{r}_0{r}^{J-1}& {r}_0{r}^{J-2}& {r}_0{r}^{J-3}& \dots & 1\end{array}\right)\end{array}\right..$$

Where *i* represents the *i* − *th* group; *j* represents the *j* − *th* stage; *k* represents the *k* − *th* group; *μ* is the grand mean; *β*_*j*_ is a fixed effect of stage *j* used to correct time trends; *δ* is the fixed effect of intervention; *X*_*ij*_ is the time-varying intervention indicator of group *i* in stage *j*; *γ*_*ij*_ is the random intercept of group *i* in stage *j*; *ε*_*ijk*_ is the individual specific random error; ***M*** is a structure matrix including two parameters; *r* and *η* are the decay rates at the cluster-period level and individual level, respectively.

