#### Open cohort stepped wedge cluster randomized trial design

For this study, *N* family branches in the Meigu and Yanyuan County will be included. Each family branch is regarded as a cluster, and *A* clusters constitute a group. It is assumed that there are *N* / *A* groups in the study, the first and third groups are in Meigu County and the second and fourth groups are in Yanyuan County. The experimental study period of the whole project is 1 year, from May 2022 to May 2023. All groups are in non-intervention during the first 3 months (Phase1) of the project. In the second 3 months (Phase2), groups 1 and 2 will start to receive intervention. Then 3 months later (Phase3), groups 3 and 4 will begin to receive intervention. According to the research proposal, all groups will continue to increase 3-month follow-up (Phase4), after all of them having received intervention in a random order, ensuring that study outcomes can be observed when time lag effect of intervention exists (Fig. 1).

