#### Outcome

The primary outcome of the project is the health literacy level of residents in the *Health Liangshan Yi Autonomous Prefecture Performance Evaluation Index*, which is defined by the 2020 *Residents Health Literacy Monitoring Questionnaire* [33].

The secondary outcomes are prevalence of hypertension, prevalence of diabetes, BMI, smoking intensity index [34], and alcohol consumption [35]. The project will measure the outcome indicators at 1, 3, 6, 9, and 12 months.

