### Sample size and sampling method

This study is an open cohort design. Since the withdrawal of the original cohort participants and the addition of new participants during the progress of the longitudinal study are allowed, the number of trial measurements may be different for each participant. Hence, after discussion with local experts, this study intends to set the participation retention rate to 0.6.

Use the formula for calculating the sample size of an open cohort SW-CRT proposed by Kasza et al. in 2020 [36], assuming that there are 50 subjects in each cluster-period, the intra-cluster correlation coefficient is 0.4, the cluster autocorrelation coefficient is 0.9, the individual autocorrelation coefficient is 0.7, the total variance is 19, and decays in between-period correlations and participant-level correlations are allowed. On the significance level α = 0.05, the 1 difference of outcome effect after intervention would be found. At the same time, in order to ensure 80% power, the minimum number of clusters required is 7.699, rounded up to 8, making the total test subjects are 400 cases. In order to take non-response into account, we expanded the sample size by 30%, and obtained 572 subjects and 11.44 clusters. After rounding the number of clusters, finally, 600 subjects from 12 family branches will participate in the study. Using R 4.0.5 to generate random numbers and assign a unique number to each recruited family branch in Meigu County and Yanyuan County. Simple random sampling will be used to select 6 family branches from Meigu County and Yanyuan County respectively, and completely randomized into 4 groups independently. In the next stage, a random sample of 50 eligible individuals will be stratified by gender and age within each family branch. The generation of random allocation sequence and allocation are completed by a third-party independent statistician.

The Meigu County and Yanyuan County carry out various health education activities for residents’ health literacy annually. This study will enrich the health literacy improvement plan under local routine management work. Due to the low education level and relatively occluded information in the study sites, it is difficult for subjects to perceive transition from the non-intervention state to the intervention state, ensuring implementation of blinding for the subjects to some extent.

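### Formula (1) is indexed on the four groups, not the twelve family-branch clusters; fitted as written, the between-unit variance rests on four units and the standard error is unstable

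*Protocol article*

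**What the plan says.** The protocol article keeps two levels apart in its stepped wedge design section. "Each family branch is regarded as a cluster", and a group is made up of several clusters. Groups, not single branches, are given the crossover times: "In the second 3 months (Phase2), groups 1 and 2 will start to receive intervention", and groups 3 and 4 follow in Phase 3.

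The section on sample size and sampling keeps the same two levels. It states that "600 subjects from 12 family branches will participate in the study", that these are "completely randomized into 4 groups independently", and that "the intra-cluster correlation coefficient is 0.4, the cluster autocorrelation coefficient is 0.9".

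The mixed-effects model section departs from this. It defines i as the group, X_ij as the intervention indicator of group i, and says that gamma_ij "is the random intercept of group" i in stage j. It labels k a group as well, yet describes epsilon_ijk as specific to the individual. It then says that r and eta "are the decay rates at the cluster-period level and individual level, respectively". The section on CACE estimation reuses formula (1) and takes its delta as the complier effect.

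**The concern.** In this article, group is a defined word for a set of branches. Under the definitions given, the unit that was sampled, and on which the correlation was planned, has no term in the primary model. An analyst who follows the text would fit random intercepts for four units, two per crossover time, where the design supplies twelve.

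At stake are the stability of the standard error, the error rate or power of the primary test, and whether the reported correlation can be set against the planning value. Because delta is reused for the CACE, the same definition governs that analysis too.

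**Working it through.** **Inputs** (sample size section unless noted): 12 branches, 4 groups, 50 residents per branch-period, ICC 0.4, cluster autocorrelation 0.9, individual autocorrelation 0.7, total variance 19, retention 0.6, target difference 1, alpha 0.05; four phases with crossovers at Phases 2 and 3 (design section). Assumed: two-sided test, three branches per group (12/4), and branch-level truth.

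**The plan's own figures.** The later steps reproduce: 8 × 50 = 400; 400/0.7 = 571.4, so 572; 572/50 = 11.44; 12 × 50 = 600. The 7.699 clusters from which they start do not: the variance below gives 30.76 clusters in total. That is a separate question. It does not affect the comparison here, which uses the same inputs at both levels.

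**Variance components.** Branch: 0.4 × 19 = 7.6. Individual: 19 − 7.6 = 11.4.

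**1. Model-based standard error with known variances.** For branch-period means:

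- variance = 7.6 + 11.4/50 = 7.828
- covariance at lag d = 7.6 × 0.9^d + 0.6 × 11.4 × 0.7^d / 50

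Generalised least squares with fixed period effects gives SE(delta) = 0.571 on 12 branch means. Averaging three branches divides the covariance matrix by 3 and leaves four units instead of twelve, so the information is unchanged and the SE on four group means is again 0.571. With balance, the level of the random effect does not bias the SE. Power for a difference of 1 is about 42% by normal approximation at either level.

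**2. What the group variance represents.** The mean of three branches has between-unit variance 7.6/3 = 2.53. The fitted group variance averaged 2.55 in simulation. As a share of the total, 2.55/19 = 0.13, where the plan has 0.4. Residents of one branch still share an intercept, but at this diluted correlation and with the whole group.

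**3. Behaviour when the variances are estimated.** Data simulated at the planning values with branch-level truth:

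| | Random effect on 12 branches | Random effect on 4 groups |
|---|---|---|
| Mean reported SE / empirical SD of the estimate | 0.537 / 0.533 | 0.528 / 0.541 |
| Coefficient of variation of the SE | 13% | 26% |
| 10th–90th percentile of the SE | 0.48–0.66 | 0.39–0.75 |
| Type I error, critical value 1.96, this run | 5.6% | 8.8% |
| Same, range over several simulations | 5.0–6.3% | 7.3–9.0% |
| Critical value, t with units minus 2 df | 2.23 | 4.30 |
| Type I error with that t | 3.1% | 0.1% |
| Power for a difference of 1 with that t | 37% | 7% |

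Except for the percentile row and the range row, the simulated figures are from 1,500 REML runs with a closed cohort, for which the known-variance SE is 0.540 and not 0.571. The Monte Carlo standard error of the 8.8% is √(0.088 × 0.912/1500) = 0.7 percentage points, and that of the 5.6% is 0.6. The percentile row and the other type I figures come from separate simulations at the same planning values.

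**4. Stage index (secondary).** The outcome section says "The project will measure the outcome indicators at 1, 3, 6, 9, and 12 months". With four three-month phases, the rounds at months 1 and 3 both fall in Phase 1. The article does not say which of them stage j = 1 refers to. No figure is attached to this.

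**The case against.** The strongest reply is that this is a labelling slip. Calling k a group cannot be meant, since the error carrying k is individual and independent between different k. The decay r acts on gamma and is described at cluster-period level, and the cluster is the branch. The planning inputs are an intra-cluster correlation and a cluster autocorrelation. On that reading the intended model already has branch effects, and the numerical harm disappears. This stands as to intent: the article does not establish that a four-unit model was chosen. It does not settle the matter, because i, X_ij and gamma_ij are all defined by group and nothing in the article corrects them.

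Stronger readings are tempting, and the documents do not support them:

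- A reader might infer that clustering within branches is ignored. It is not: the group intercept carries a diluted part of it, and the SE is not biased on average in a balanced design.
- A reader might infer that the false-positive rate is necessarily inflated. That depends on a z reference. The article names no reference distribution and may leave it to the analysis plan; with t on two degrees of freedom the test is conservative and power is lost instead.
- A reader might infer that residents have no index. In use, k is the resident; only its label is wrong.
- A reader might infer that the spacing of the rounds invalidates the decay structure. Months 3, 6, 9 and 12 are equally spaced, and only month 1 is off the grid. How it enters the model is a matter for clarification.

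**Conclusion.** The definitions under formula (1) conflict with the design section, with the sample size and with their own description of r and k. They need correcting because they specify the primary model and, through delta, the complier effect.

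Taken literally, the cost is loss of stability and degrees of freedom, not a biased standard error: the variation of the SE doubles. The test then has either a type I error some two to three percentage points higher than with branch effects (z) or little power left (t on four units).

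The size of this rests on the planning values, three branches per group, balanced branch sizes and branch-level truth. If i was always meant as the branch, there is no numerical harm and only the wording is at fault.

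**What to change.** In the definitions under formula (1):

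- let i be the family branch, 1 to 12, and k the resident;
- let gamma_ij be the branch-by-period random effect;
- let group enter only through X_ij, by setting the crossover time of its branches.

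State that the same definitions apply where delta is taken as the CACE. Use a small-sample reference distribution suited to 12 clusters, in the article or in the analysis plan. The simple t on 10 degrees of freedom tried here was somewhat conservative, at 3.1%, so the choice should be checked by simulation at the planning values. Add one sentence saying how the month-1 and month-3 rounds map to stage j.

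The cost is a few lines of text and a short simulation before analysis. Recruitment, randomisation and data collection are unaffected.

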#### Adopt causal inference model to deal with non-compliance issues

SW-CRT can observe participants’ compliance under intervention and control conditions [38, 39]. Therefore, we would divide the participants into four subgroups based on their compliance, as shown in Table 1. *D*_*i*_(0) and *D*_*i*_(1) represent that individual *i* is divided into control group and treatment group, respectively. *D*_*i*_ = 0 and *D*_*i*_ = 1 represent individual *i* actually accept control and actually accept treatment, respectively.

**Table 1 Tab1:** Treatment Usage by Subgroup Classification

Behavior	Subgroup
*D*_*i*_(0) = 0, *D*_*i*_(1) = 1	Complier
*D*_*i*_(0) = 1, *D*_*i*_(1) = 1	Always-taker
*D*_*i*_(0) = 1, *D*_*i*_(1) = 0	Defier
*D*_*i*_(0) = 0, *D*_*i*_(1) = 0	Never-taker

Below, lay out the steps we followed to identify and estimate complier average causal effects (CACE) in our SW-CRT.

##### Treatment of interest

In this study, we attempt to identify the effect of compliance with Yi nationality residents in Liangshan Prefecture through the health literacy intervention based on Family Branch System.

##### Causal model of compliance & classification of subgroups

In our study, the control group can be treated, so we construct subgroup classifications based on cumulative behaviors to account for time-varying treatment-usage patterns. We will divide participants into four subgroups, including Complier, Always-taker, Defier, and Never-taker.

##### Equivalence of comparison groups

To check for balance in observable characteristics among compliers, calculate a weighted average of baseline characteristics by the amount of time a Family branch spent in either control or intervention time periods. For example, if a Family branch crossed over in step *a*(0 < *a* < *n*), it contributed baseline characteristics to *a* control periods (step 0~*a* − 1) and *n* − *a* + 1 intervention periods (step *a*~*n*).

##### CACE estimation

We will estimate inter-group differences in time-dependent SW-CRT for outcomes:2$$E\left[Y|A=1,T=t,C=1\right]-E\left[Y|A=0,T=t,C=1\right],$$where *Y* is the outcome; *A* is an indicator, *A* = 1 is the treatment group, *A* = 0 is the control group; *T* represents time; *C* is an indicator of being a complier (*C* = 1). Under the above assumptions, we supposed *C* is a preexisting characteristic and is stable throughout the study period. The estimation of step-specific CACE can be averaged over all steps to avoid the impact of time and interventions.

We assume that the intervention prior to step *t* does not affect outcomes at step *t* and the intervention effects are constant (*E*[*Y*| *A* = 1, *T* = *t*, *C* = 1] − *E*[*Y*| *A* = 0, *T* = *t*, *C* = 1] is not a function of *t*). Then the estimation of step-specific can be averaged of the effect across all intervention steps:3$$\frac{1}{n}\sum \limits_{i=1}^n\frac{1}{s}\sum \limits_{t=0}^sE\left[{Y}_i|{A}_i=1,{T}_i=t,C=1\right]-E\left[{Y}_i|{A}_i=0,{T}_i=t,C=1\right],$$where *n* is the total number of participants; *s* is the total number of steps.

The behaviors of participants were observable in SW-CRT. So, we can estimate CACE according to mixed-effects model based on the outcomes of complier. As shown in formula (1), *δ* is CACE.

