##### Step 2. Promotion within family branch

The sponsor of each famliy branch will use the health literacy knowledge brochures to educate other members in famliy branches on health literacy according to the operating manual. We encourage all members of famliy branches to participate in the project, identify problems, propose and implement solutions, conduct self-evaluation and measure improvement. Besides, we require each famliy branch to hold at least one collective sharing meeting monthly.

In terms of nutrition education, we will design and produce nutrition education playing cards in the form of popular 4 or 6 sentences, which are repeatedly revised and proven by a number of nutrition experts. The contents mainly include Chinese dietary guidelines and balanced diet pagoda, the function of nutrients and their main food sources, the nutritional value of various foods, dietary guidance for specific populations and patients with common NCDs, aerobic exercise, weight evaluation and its impact on health, food safety problems, the harm of excessive smoking and drinking, etc. The nutrition education methods will include the following: (1) Distribute nutrition education cards, introducing their main contents and carrying out a quiz on the contents of the cards. Train the sponsors to explain the cards to other family members through their publicity. (2) Distribute nutrition health knowledge publicity materials, and ask the use of the cards to supervise. (3) Set up nutrition knowledge bulletin boards and post nutrition health knowledge bulletin materials. (4) Start nutrition knowledge courses and lectures. (5) Set up personalized online or offline nutrition counseling and guidance stations which are mainly based on the actual dietary situation of the residents, and provide relevant dietary nutrition guidance after analysis.

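### Phase 4 is added in case the effect lags, but the analysis assumes an immediate, constant effect; if the effect builds up, the single estimate is biased toward zero and, in an extreme case, negative

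*Protocol article*

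**What the plan says.** In the Protocol article, the section on the open cohort stepped wedge design sets two crossover dates: "In the second 3 months (Phase2), groups 1 and 2 will start to receive intervention" and "Then 3 months later (Phase3), groups 3 and 4 will begin to receive intervention". A further 3-month Phase 4 follows, with the stated purpose of "ensuring that study outcomes can be observed when time lag effect of intervention exists".

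The mixed-effects model section gives formula (1): a fixed effect for each stage, a branch-by-stage random effect, an individual error, and one coefficient δ on a 0/1 intervention indicator. It has no term for time since crossover and no transition period.

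The CACE estimation section then assumes that intervention before a given step leaves the outcome at that step unaffected "and the intervention effects are constant". It uses the same coefficient for compliers: "As shown in formula (1), *δ* is CACE".

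Delivery is repeated. Under Step 2 of the intervention, "we require each famliy branch to hold at least one collective sharing meeting monthly", and Step 3 adds recurring competitions between branches.

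**The concern.** The design section provides for a delayed effect and the analysis section rules one out. Both are written rules of the plan, so this is not detail left to a separate analysis plan.

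The layout makes the conflict matter. Phase 1 is all control, Phases 3 and 4 are all intervention, and only Phase 2 has both conditions at once. A constant-effect model expects no difference between early and late branches in Phases 3 and 4, because all are treated. It takes any gap there as a sign of pre-existing branch differences and subtracts part of it from the Phase 2 contrast. If the effect grows with exposure, that gap is itself intervention effect, because the early branches are one phase ahead. The estimate and the CACE built on it would then understate a real benefit.

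**Working it through.** **Inputs.** From the sample size section: 50 subjects per branch-period, intra-cluster correlation 0.4, cluster autocorrelation 0.9, individual autocorrelation 0.7, total variance 19, retention 0.6, α = 0.05, 12 branches. From the design section: indicator patterns 0,1,1,1 (early) and 0,0,1,1 (late).

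**Assumptions made here.** Six branches per sequence, one measurement round per phase, retention 0.6 at every lag, and a two-sided test with a normal reference.

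**Covariance of branch-period means.** Cluster part 19 × 0.4 = 7.6; individual part 11.4/50 = 0.228.
- Variance: 7.6 + 0.228 = 7.828
- Lag 1: 7.6 × 0.9 + 0.6 × 0.7 × 0.228 = 6.936
- Lag 2: 7.6 × 0.81 + 0.6 × 0.49 × 0.228 = 6.223
- Lag 3: 7.6 × 0.729 + 0.6 × 0.343 × 0.228 = 5.587

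The protocol gives no figure for this point. As a check on the covariance, three periods give 30.79 branches for 80% power, and 30.79/4 = 7.70, which matches the protocol's 7.699. What that implies for sample size is a separate matter.

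**Weights.** With stage effects fitted, δ depends only on the early-minus-late gap in each phase. The indicator gap is x = (0,1,0,0), and the generalized least squares weights are x′V⁻¹ / (x′V⁻¹x) = −0.493, 1.000, −0.472, −0.025 for Phases 1 to 4.

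**Expected estimate.** Let θ1, θ2 and θ3 be the effects in the first, second and third phase of exposure. Early branches then carry (0, θ1, θ2, θ3) and late branches (0, 0, θ1, θ2), so the gap is (0, θ1, θ2−θ1, θ3−θ2). Hence

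E[δ] = θ1 − 0.472(θ2−θ1) − 0.025(θ3−θ2) = 1.472θ1 − 0.448θ2 − 0.025θ3.

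The coefficients sum to 1 apart from rounding, so a constant effect is recovered. Later effects enter with a negative sign.

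| Assumed θ1, θ2, θ3 | Expected δ |
|---|---|
| 1, 1, 1 | 1.00 |
| 0.8, 1, 1 | 0.71 |
| 0.5, 1, 1 | 0.26 |
| 1/3, 2/3, 1 | 0.17 |
| 0, 1, 1 | −0.47 |

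With θ2 = θ3, the expectation is negative only if θ1/θ2 < (0.448 + 0.025)/1.472 = 0.32.

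**Precision and power.** x′V⁻¹x = 1.0206. With six branches per sequence, Var(δ) = 1/(3 × 1.0206) = 0.327, so SE = 0.57. The chance of a significant benefit is about 42% under a constant effect of 1, 23% with 80% present at once, 7% with half, and 0.3% with a full one-phase lag.

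**Exposure-time fit.** With δ_1, δ_2, δ_3 in place of δ, all three are estimable, with SEs 0.75, 1.57 and 2.50.

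**Sensitivity.** The variants were five measurement rounds, retention compounding by lag, ICC down to 0.01, cluster autocorrelation 0.5, and block-exchangeable correlation. Across them the half-lag value stays between 0.26 and 0.37 and the full-lag value between −0.27 and −0.49. Simulation with 12 branches gave means of 1.01, 0.26, 0.17 and −0.47 for the constant, half-lag, linear and full-lag cases.

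**The case against.** A single intervention indicator with stage effects is an ordinary working model, and the protocol states its assumption openly. Four points on that side deserve weight.

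- A reader might infer that the design expects a lag. It does not: the wording is conditional, and no size or shape is given. The profiles above are assumptions, and repeated meetings show repeated delivery, not a growing effect.
- A reader might infer that the trial will report a wrong sign. The documents do not support that. The 0, 1, 1 case needs no gain on the questionnaire after about three months of training, brochures and meetings, then the full gain. Milder profiles shrink the estimate without reversing it in expectation.
- It is tempting to make the first-phase effect δ_1 primary. That is the effect before any lag has passed: under 0, 1, 1 its expectation is zero, so the benefit is still missed. Power for an effect of 1 falls from about 42% to 27%. Judged as an estimate of δ_1, the constant-effect fit even has the smaller mean squared error: 0.38 (half lag) and 0.55 (full lag), against 0.75² = 0.56.
- Dropping the assumption altogether would leave the CACE without a definition.

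These points limit the claim and the remedy. They do not remove the conflict between the two sections, or the negative weights that follow from the layout.

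**Conclusion.** The concern holds in this form: the plan provides for a lag in its design and excludes one in its analysis, and with a single concurrent phase the single δ is biased toward zero if the effect builds up. The loss is about 30% if four fifths of the effect is present in the first phase and about three quarters if half is. A negative expectation needs a first-phase effect below about one third of the later one. If the effect is immediate and constant, there is no bias.

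Phase 4 does little to help under formula (1): its gap carries a weight of −0.025. The CACE uses the same treatment coding and the same single concurrent phase, so it shares the problem, although its exact weights would change with the number of compliers per branch.

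The sizes rest on the protocol's planning correlations and on lag profiles assumed here.

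**What to change.** 1. Reconcile the design and CACE sections: the assumptions of no carry-over and a constant effect should no longer be a basis for the trial's conclusion.
2. Pre-specify, alongside formula (1), a fit that replaces δX_ij by δ_1, δ_2 and δ_3 for the first, second and third 3-month phase since crossover, reported with intervals.
3. State that the single δ, and the CACE taken from it, can be read as the intervention effect only if the effect does not change with exposure time.
4. State that this two-crossover layout gives little information on effects beyond the first 3 months.

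The change is to the analysis text. It needs no new data, and the protocol reports that recruitment was still being prepared. The cost is candour about precision: with 12 branches, power for a true effect of 1 is about 27%, 9% and 6% for δ_1, δ_2 and δ_3. The extra fit will show whether the data are compatible with a build-up, but it will seldom settle the matter. Three crossover dates in the same rounds would bring the SEs of δ_1 and δ_2 to 0.58 and 1.09, but that is a change of design and goes beyond this point.
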